## Abstract

**Background:**

An adolescent's school is often the second most important place for his development and education after the home. However, reports highlight the recurrence of the use of violent discipline in schools. There are few school-based interventions that aim at reducing violence at school that have been implemented and evaluated in sub-Saharan Africa. To reduce violent disciplinary measures used at school, we aim to implement and evaluate the feasibility and efficacy of the preventative intervention *Interaction Competencies with Children for Teachers (ICC-T)*.

**Methods/design:**

The study will be conducted in six randomly selected districts of the Ankole region in southwestern Uganda. We shall randomly select two mixed-day secondary schools from each district that fulfill our inclusion criteria. Schools will be randomly assigned to the intervention condition, where ICC-T will be implemented, and control schools (no intervention). Sixty students between the ages of 12 and 17 years and at least 15 teachers per school will be included in the trial. We aim to collect pre-assessment data directly before the intervention (t1) and 3 months after the intervention (t2) in both intervention and control schools.

Using self-administered questionnaires, we will measure students’ exposure to violence using the Conflict Tactics Scale (CTS), their psychological well-being using the Strengths and Difficulties Questionnaire (SDQ), and teachers’ positive attitudes towards violent disciplining and teachers’ use of violent disciplinary methods (CTS). The implementation feasibility of ICC-T in the cultural context of southwestern Uganda will be assessed with purpose-built measures that follow the guidelines for feasibility studies assessing the demand, applicability, acceptability, and integration of core elements in the daily work.

**Discussion:**

The proposed study will allow us to test the feasibility and efficacy of a preventative intervention seeking to reduce violent disciplinary measures in school settings using a scientifically rigorous design. The proposed study provides the opportunity to contribute to the attainment of goal number 16.2 of the United Nations’ Sustainable Development Agenda 2015–2030, which aspires to end all forms of violence against children.

**Trial registration:**

ClinicalTrials.gov, NCT03051854. Registered on 14 February 2017.

**Electronic supplementary material:**

The online version of this article (10.1186/s13063-018-2827-9) contains supplementary material, which is available to authorized users.

## Background

Violent disciplinary measures refer to the deliberate use of physical force that results in bodily and/or emotional pain with the aim of correcting or regulating a child’s behavior in the school setting [1]. Violent disciplinary measures are prevalent worldwide and take diverse forms, including the use of hands or objects, such as a cane, whip, or stick, by teachers and school staff to inflict bodily pain on the students [2]. Other forms of punishment include flogging, lashing, shaking, scratching, kicking, and pinching. Maintaining a seated position on an imaginary chair for long periods of time and adoption of bodily postures that cause enormous pain are other examples of methods of physical punishment used in the school setting [3]. In educational settings students can be exposed to violence, which may result in a variety of negative outcomes, including fear of the school staff, emotional problems, physical injuries, and mental health problems which, in the long term, may affect academic achievement [4].

### Global perspective on violence by teachers

Worldwide, the use of physical violence by teachers is legally accepted as a disciplinary measure in 68 countries [5]. Africa accounts for 40% of all countries globally which lawfully allow physical punishment in the education context. Students experience violence at school, especially in the USA and in Asian and African countries [3, 6, 7]. Providing global estimates of physical violence at school using data from 63 countries from Asia, Africa, Europe, and North and South America, one research report noted that the prevalence rates were between 13% and 97% among 29 countries with legislation that prohibits the use of corporal punishment in school, while 20 countries that do not prohibit violence by teachers in school had prevalence rates between 70% to 98%. Rates of physical violence at school were generally higher in low- and middle-income countries [3].

Despite the legal framework that prohibits physical violence at school, its use continues in many countries. This could be due, for example, to a lack of proper implementation of appropriate laws. Though many countries have enacted laws that forbid physical violence at school, they have failed to stipulate alternative forms of disciplinary procedures applicable in the school setting to guide teachers and students. This contradiction has resulted in teachers’ reliance and continued exclusive use of violent punishment as a disciplinary measure. Furthermore, there are many countries in which violent discipline is still legal [3, 8, 9].

### Violence by teachers in sub-Saharan African countries

Research reports have documented particularly high prevalence rates of violent punishment in sub-Saharan Africa. In total, 27 countries do not fully forbid physical and emotional violence by teachers, which increases the likelihood of students experiencing violence at school [3, 5]. Rates of violent punishment in 22 selected African countries (12 states that allow corporal punishment) range from 98% among boys and 91% of girls in Tanzania to 28% of students in Djibouti [3]. One study conducted among 42 primary schools in Ghana, Kenya, and Mozambique revealed that 80–90% of students experienced physical violence at school in the past year [10]. More than 52% of students experienced violence at school in West and Central African countries including Benin, Senegal, the Central African Republic, and Gambia [11]. Moreover, about half of in-school adolescents experienced physical violence in Namibian schools [12].

Violent disciplinary measures are used when students violate school norms, perform poorly, or make noise in class [3, 7]. Teachers justified the use of violence in the context of child discipline procedures and as a way of exercising power, compliance, and behavioral control [13]. Teachers preferred the use of corporal punishment because they perceived it to be an effective discipline measure that results in immediate compliance. In spite of their use of corporal punishment, teachers were not aware of the consequences associated with the use of violence and lacked knowledge of other effective discipline alternatives [14]. As a consequence, positive attitudes towards corporal punishment may result in the continuation of violence by teachers at school [13].

### Current situation in Ugandan schools

The use of violence at school in Uganda is prohibited by laws, policies, and guidelines, including the Teachers’ Professional Code of Conduct [15], the penal code of Uganda laws, the Education Act, and the Ministry of Education and Sports guidelines [16, 17]. Physical punishment was suspended in schools and colleges by 1997 and finally abolished in 2006 by the Uganda Ministry of Education and Sports; nevertheless, the use of corporal punishment still frequently occurs in the education setting to date [17].

One survey of 25 schools across five districts in Uganda found that 81% of the children had experienced physical violence at school [18]. More than 90% of primary school pupils had been exposed to physical and emotional violence at school [4]. Students experienced teacher-inflicted physical violence on an almost weekly basis [19]. These findings underline the fact that legislation has not resulted in the overall elimination of violence by teachers in Uganda.

### Consequences of violence by teachers at school

School violence is a painful experience associated with physical injuries [20, 21], child aggression and antisocial behavior [22], externalizing and internalizing behavioral problems [4], and depression and post-traumatic stress disorder (PTSD) symptoms [23–25]. Research findings also emphasize that students who have been victims of violence at school showed lower self-esteem, engaged in destructive avoidance behavior, and limited their communication strategies in the school locale [14]. In accepting violence as the normative disciplinary measure, students do not understand that the use of violent disciplinary measures is a violation of their rights [20].

Furthermore, the use of violence in the school leads to chronic fear of violent teachers as well as school avoidance [14]. Consistently, violence by teachers at school has resulted in negative education outcomes, such as low education achievement and school absence [21], poor academic performance, and increased school drop-out rates and absenteeism [18, 20].

### School-based violence prevention interventions

The use of physical violence is further reinforced by sociocultural norms that justify its use as a disciplinary method. Hence, there is a pressing need to reduce children’s exposure to violence, especially in the school setting [3]. This calls for prevention approaches against the use of violence by teachers at school.

Human rights activists at the global level have been at the forefront of advocating for the ban of corporal punishment [8]. For example, the United Nation’s Sustainable Development Goal Number 16.2 seeks to put an end to all kinds of violence against children by 2030 [26]. The African Union, in the same vein, seeks to protect children from violence. For example, the African Committee on the Rights and Welfare of Children envisaged that by the year 2020 countries in Africa ought to have outlawed the use of violence in the education sector and anticipate that by 2040 there will be no child who experiences violent disciplinary measures in any setting [27]. However, the focus so far has been mainly on the legislative aspect.

Thus, interventions that aim at preventing violence while changing attitudes and behavior in relation to violence become a necessity, particularly in contexts in which the use of violence is the norm rather than the exception [3]. Interventions that include training aspects for teachers seem to be successful in reducing violence at school. Recommended training content includes non-violent corrective approaches.

However, there are very few interventions, especially in low-income countries, that have been evaluated for their efficacy. For example, one study in South Africa examined the consistency between the disciplinary approaches used in the schools and the tenets of alternatives to corporal punishment. Generally, the implementation of alternative disciplinary strategies was hindered by the lack of formal training of educators in these methods and inadequate consultations with education stakeholders. Despite the noted challenges, alternatives to physical punishment resulted in better discipline among learners, provided teachers with more non-violent discipline choices, accorded students the opportunity to explain as much as possible for any noted behavioral deviations, and built a school culture based on self-discipline and non-violence [28].

In Uganda, the use of violent disciplinary approaches in schools is legally not permitted; however, teachers are not formally provided with alternative disciplinary strategies applicable in the education sector [15]. Positive disciplinary approaches [17] appropriate for schools in handling student discipline-related concerns have been proposed. These include reflection to tackle minor problems, penalties for persistent problems, suspension for offenses that cause damage to others and property, and as a last resort, suspension for consistently serious wrongdoings.

The Good Schools Toolkit intervention designed to prevent physical punishment against students has been evaluated in 42 Ugandan schools [29]. The kit engages stakeholders including teachers, students, parents, and school administrators in advocating for the use of non-violent discipline techniques as a way of fostering a better learning environment and mutual respect in schools among others. The study evaluated the implementation of the Good Schools Toolkit in primary schools in Luwero District in the Central Region of Uganda. In a cluster randomized controlled trial the Good Schools Toolkit intervention resulted in a significant reduction (42%) of teacher-initiated physical violence against students [21]. At follow-up, school staff reported using less violence in the past week at intervention schools (16%) than at control schools (33%; odds ratio 0.39, 95% confidence interval 0.20–0.73). The prevalence of past week physical violence reported by students was also lower in the intervention schools (31%) than in the control schools (49%; odds ratio 0.40, 95% confidence interval 0.26–0.64).

To the best of our knowledge, there is as yet no school-based violence prevention intervention that has been implemented and evaluated for its efficacy at the secondary school level in Uganda. The preventative intervention *Interaction Competencies with Children (ICC)* aims to foster better adult-child interactions while reducing the occurrence of violent discipline. There are currently two versions of ICC, one for caregivers (ICC-C) and one for teachers (ICC-T) [30–33]. ICC-T aims to contribute to the reduction of violence so that students do not experience emotional and physical violence at school in the long term [34]. In East Africa, ICC-T has been successfully implemented and evaluated for its feasibility and efficacy in a cluster randomized controlled trial in secondary schools [30] as well as for its feasibility at the primary school level in Tanzania [31]. The study at primary school level revealed that teachers who participated in the ICC-T program found the intervention content to be relevant for their work and were able to integrate the ICC-T tenets, such as alternative discipline methods, into their daily working routine. ICC-T resulted in better teacher-student relations, less physical violence by teachers, and improved student behavior in the follow-up assessment [31]. On the secondary school level, a cluster randomized controlled trial was implemented: eight schools were randomly assigned as intervention and control schools. Results showed that the participating teachers reported a high acceptance of the intervention and a good integration of ICC-T content into their daily work. At follow-up, there was a substantial difference in the use of both emotional and physical violence by the teachers as reported both by students (emotional violence: effect size Cohen's *d* = 0.94; physical violence: effect size partial η^2^ = .06 after controlling for difference at baseline) and teachers (emotional violence: *d* = 1.56; physical violence: *d* = 1.38). Teachers’ positive attitudes towards violence were also lower in the intervention schools at follow-up (emotional violence: *d* = 1.17; physical violence: *d* = 0.96) [30].

Encouraged by these promising initial results, in our current study we aim to evaluate the feasibility and efficacy of ICC-T at the secondary school level in southwestern Uganda. The implementation of ICC-T in Uganda builds upon previous knowledge, because ICC-T focuses on both physical violence and also emotional violence—the most common types of violence that co-occur in the school setting in Uganda [18, 19]. Moreover, during the interactive training phase, the views and needs of the teachers are incorporated into the training.

### Objectives

The use of violent discipline strategies has continued in Ugandan schools to date despite guidelines that hinder the use of punitive correction approaches. This has been complicated by strong cultural beliefs and support for the use of violence in schools and the general lack of formal alternatives to physical punishment that can help teachers to handle student discipline concerns. To address this challenge, we will implement and evaluate the feasibility and efficacy of ICC-T as a violence prevention approach in secondary schools in southwestern Uganda. With ICC-T our goals are to change teachers’ attitudes concerning the use of violent disciplinary measures, reduce the use of harsh and violent disciplinary measures in schools, and foster better interactions between students and teachers.

## Methods/design

### Study design

In a two-arm cluster randomized controlled trial, 12 secondary schools will be randomly assigned to the intervention group (which will receive the ICC-T intervention training) or the control group (which will receive no training). The study will have two data collection points: pre-assessment and follow-up assessment. See Figs. 1 and 2 and the Standard Protocol Items: Recommendations for Interventional Trials (SPIRIT) checklist (Additional file 1).

**Fig. 1 Fig1:**
[figure not shown]
Flow chart of the study design

**Fig. 2 Fig2:**
[figure not shown]
Participant timeline chart

### Study setting

In Uganda, primary school takes 7 years, secondary school (ordinary level) 4 years, and high school (advanced level) 2 years. The education sector in Uganda is divided into 13 regional clusters, with each cluster having seven to 15 districts. Southwestern Uganda has two regional blocks: Ankole and Kigezi. This study will be conducted in Ankole region. Ankole has the third highest student enrollment in Uganda with 134,509 students (50% males), and the majority of the secondary school students (47%; *n* = 62,807) studying in *Senior One* and *Senior Two* (8th and 9th years of formal schooling). The region has 10 districts with each district having 3–20 government-aided secondary schools.

Ankole region was purposefully selected because it has the second largest number of government-aided secondary schools (117), with 96 of those implementing the free Universal Secondary Education (USE) government program. Government-aided schools implementing the USE program as a matter of policy are expected to have at least two streams with 60 students per stream. This translates to a minimum secondary school student population of 720 students [35].

The Ministry of Education, Science, Technology and Sports reports that there were only 80 mixed secondary schools that implemented the USE program in the region, which included the number of classes, school enrollment, and number of teachers [35, 36]. Ankole region has 3460 teachers employed in the various schools. The 117 government-aided secondary schools in the region have on average about 25 teachers [36].

### Schools

We plan to include 60 students (30 in 8th year and 30 in 9th year of formal schooling) per school. Based on previous studies in similar settings, we expect a participation rate of approximately 50% [23, 37–39]. This means that we will include schools that have a minimum student enrollment of 60 per year of study, i.e., 360 students in total.

Furthermore, as ICC-T intervention is a participatory approach that involves active engagement and practical hands-on learning, we consider ICC-T workshops to be cost-effective with a minimum number of at least 15 participants. That is why we will include only schools that employ at least 15 teachers. Only 41 schools fulfilled these inclusion criteria.

Additionally, we aim to select at least two schools per district in order to randomly assign them into the intervention or control conditions. Eight districts, i.e., Bushenyi, Ibanda, Isingiro, Kiruhura, Mitooma, Ntungamo, Mbarara, and Sheema, have at least two eligible schools. Given that Mbarara district is more like the “regional capital” of the Southwestern region, we purposefully included this district in the study sample. We then randomly selected five districts from the remaining seven districts. In the event that the selected district has two eligible schools, these schools are automatically included in the study sample. From districts that had three to 11 eligible schools, only two schools are randomly selected. As a result, the final sample consists of 12 coeducational secondary schools, from six different districts: Ibanda, Isingiro, Kiruhura, Mitooma, Ntungamo, and Mbarara.

### Participants

Due to the longitudinal nature of the study which necessitates two data collection points, the focus of this study is on students in the 8th and 9th years of formal schooling. Based on a previous study that used a similar design to test the efficacy of ICC-T in Tanzania [30], we would expect a moderate to large effect on students’ self-reported exposure to violence. An a priori power analysis (α = .05, power = 0.80, moderate effect size of ƒ = 0.25) using G*Power software [40] indicated a required total sample size of at least *n* = 128 students to detect significant interaction effects. To adjust for the nested design of the study, we calculated the following design effect (DE): DE = 1 + (fixed cluster size considering drop-outs − 1) × intra-cluster correlation coefficient. Considering 60 students per school, a drop-out rate of 20%, and an intra-cluster correlation coefficient of 0.05, the DE for the student sample is 3.35, which results in a required sample size of at least 430 students. We aim to randomly select, at each school, 30 students from Senior One (8th year) and 30 from Senior Two (9th year). The target sample will thus be 720 students in the age range between 12 and 17 years. At the classroom level a list of all students will be obtained from the school administration. Stratified random sampling will be used to select 15 boys and 15 girls from each class or stream.

All teachers who are officially working in the selected schools will be included in the study sample. Based on the previous study in Tanzania [30], we would expect a large effect on teachers’ self-reported use of violence against students. An a priori power analysis (α = .05, power = 0.80, moderate to large effect size of ƒ = 0.35) using G*Power software [40] indicated a required total sample size of at least *n* = 67 teachers to detect significant interaction effects. To adjust for the nested design of the study, we again calculated the DE. Considering a minimum of 15 teachers per school, a drop-out rate of 20%, and an intra-cluster correlation coefficient of 0.05, the DE for the teacher sample is 1.55, which results in a required sample size of at least 104 teachers. Our target sample will be at least 15 teachers per school, resulting in a total sample of at least 180 teachers.

Only selected students aged 12–17 years and teachers in the age range 18–65 years, employed by the selected schools and who will be present during the data collection period, will be included in the study. Teachers will be enrolled in the study if they give their informed consent. Students with parental informed consent and who freely provide assent will be accepted to participate in the study. Students and teachers with acute psychotic symptoms or acute alcohol or drug intoxication will be excluded from the study.

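### The minimums of 430 students and 104 teachers ignore how few schools are randomised: at the cluster sizes behind their design effects they equal about 9 schools, with power near 0.68 and 0.71 rather than 0.80

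*Protocol article*

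**What the plan says.** The Study design section makes the school the unit of allocation: "12 secondary schools will be randomly assigned to the intervention group" or to control. The Discussion gives six schools per arm.

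The sample-size argument is in the Participants section. For students, a G*Power calculation ("α = .05, power = 0.80, moderate effect size of ƒ = 0.25") "indicated a required total sample size of at least *n* = 128 students to detect significant interaction effects". Nesting is then handled with the formula "DE = 1 + (fixed cluster size considering drop-outs − 1) × intra-cluster correlation coefficient". The inputs are these: "Considering 60 students per school, a drop-out rate of 20%, and an intra-cluster correlation coefficient of 0.05". The result is that "the DE for the student sample is 3.35, which results in a required sample size of at least 430 students". The target is 720 students.

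For teachers the same steps use f = 0.35, an individual-level n of 67, at least 15 teachers per school, 20% drop-out and a correlation of 0.05, so that "the DE for the teacher sample is 1.55, which results in a required sample size of at least 104 teachers". The target is at least 180 teachers.

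**The concern.** A design effect converts a number of individuals into an effective number of independent individuals. It does not change the reference distribution of the test. The starting figures of 128 and 67 assume well over sixty error degrees of freedom. A comparison of arms that respects school randomisation has schools − 2, which is 10 in the planned trial and fewer in anything smaller. With so few clusters the difference is material: the two-sided 5% critical t is 2.36 on 7 degrees of freedom, against 1.98 on 126.

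The article presents 430 and 104 as enough for 0.80 power. Anyone who later uses them to judge how much loss is tolerable, or how informative a null result is, would credit a sample of that size with power it does not have at the cluster sizes used to derive it.

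**Working it through.** **Inputs, all from the Participants section.** α = 0.05; target power 0.80; f = 0.25 (students) and 0.35 (teachers); 60 and 15 enrolled per school; 20% drop-out; intra-cluster correlation (ICC) 0.05. Analysed per school: m = 60 × 0.8 = 48 and 15 × 0.8 = 12.

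**Step 1: reproduce the article's figures.** Use the noncentral F with 1 numerator degree of freedom and noncentrality λ = N × f². The smallest N reaching 0.80 is 128 at f = 0.25 (126 error df, power 0.801) and 67 at f = 0.35 (65 error df, power 0.806). The error df are inferred from this match; a four-group variant (124 and 63) gives the same N.

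- Students: DE = 1 + 47 × 0.05 = 3.35; 128 × 3.35 = 428.8 (stated 430).
- Teachers: DE = 1 + 11 × 0.05 = 1.55; 67 × 1.55 = 103.85 (stated 104).

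The multiplication is sound.

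**Step 2: convert the minimums to schools.** Because cluster size is defined after drop-out, 430 and 104 are read as analysed numbers. 430 / 48 = 8.96 and 104 / 12 = 8.67, so about 9 schools in each case.

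**Step 3: power on school-level degrees of freedom.** For k schools, λ = (k × m / DE) × f², with k − 2 error df. For 9 schools:

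- Students: 432 / 3.35 × 0.0625 = 8.06, power 0.684.
- Teachers: 108 / 1.55 × 0.1225 = 8.53, power 0.708.

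Exactly 430 and 104 on 7 df give 0.682 and 0.692. A 4 v 5 split of nine full schools gives 0.679 and 0.703.

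| Schools | df | Students analysed | Power | Teachers analysed | Power |
|---|---|---|---|---|---|
| 9 | 7 | 432 | 0.684 | 108 | 0.708 |
| 10 | 8 | 480 | 0.746 | 120 | 0.769 |
| 11 | 9 | 528 | 0.797 | 132 | 0.819 |
| 12 | 10 | 576 | 0.839 | 144 | 0.859 |

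At these cluster sizes, 0.80 needs 12 schools for students and 11 for teachers.

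**Step 4: hold 12 schools fixed and vary cluster size.** On 10 df, λ must reach 9.67.

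- The stated minimums spread evenly: 430 / 12 = 35.8 per school, DE 2.74, power 0.805. 104 / 12 = 8.7 per school, DE 1.38, power 0.781.
- The smallest totals reaching 0.80: students 414 (34.5 per school, DE 1 + 33.5 × 0.05 = 2.675, λ = 414 / 2.675 × 0.0625 = 9.67). Teachers 112 (9.33 per school, DE 1 + 8.33 × 0.05 = 1.417, λ = 112 / 1.417 × 0.1225 = 9.68).

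**Step 5: sensitivity to the ICC, all 12 schools.** At ICC 0.10 the design effects are 1 + 47 × 0.10 = 5.70 and 1 + 11 × 0.10 = 2.10. Then λ = 576 / 5.70 × 0.0625 = 6.32 (power 0.62) and 144 / 2.10 × 0.1225 = 8.40 (power 0.74). Student power falls below 0.80 once the ICC exceeds about 0.058.

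**The case against.** The strongest reply is that no nine-school trial is planned. The article fixes 12 schools and reports that all of them agreed to take part. Nine appears only when 430 is divided by 48. Spread over 12 schools, 430 students do reach 0.805, and 104 teachers miss by only two points. All of this stands, and it rules out any claim that the planned trial lacks power. It does not rescue the printed calculation. Power of 0.805 arises with a design effect of 2.74, not the stated 3.35, so for students an overstated variance inflation happens to offset the missing small-cluster allowance. For teachers it does not quite do so.

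A second reply is that the Analysis section moves to multilevel analysis only if the ICC exceeds .10, so at 0.05 the planned MANOVA would itself use individual-level degrees of freedom. That is true, but school-level degrees of freedom are what a valid test of a school-randomised effect requires, and power should be judged on them.

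A reader might also infer that the teacher calculation is unsafe because it uses the eligibility minimum of 15, whereas "The 117 government-aided secondary schools in the region have on average about 25 teachers". The design effect would indeed be larger with 25 per school (20 analysed: 1 + 19 × 0.05 = 1.95). But with the number of schools fixed, larger clusters raise power: 0.94 in 12 schools and 0.87 in 10. Planning on 15 is conservative. The regional average also covers all government-aided schools, not the selected ones.

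Finally, the article never says that schools can be lost; a three-school margin is only what the figures invite a reader to assume.

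**Conclusion.** The point holds for the stated minimums only. At the cluster sizes that generate the design effects of 3.35 and 1.55, 430 students and 104 teachers correspond to about 9 schools, with power of about 0.68 and 0.71 against the stated 0.80. The full design is adequate under the article's own assumptions, at 0.84 and 0.86.

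What misleads is the apparent margin. Losing students evenly within all 12 schools is tolerable down to about 414 analysed. Losing schools is not: one lost school brings student power to 0.797, and two bring it to 0.746. Teacher power stays at 0.819 with 11 schools and falls to 0.769 with 10, at 12 analysed per school.

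These figures assume the article's f values, equal cluster sizes, equal arms except where a split is named, no gain from matching or baseline adjustment, and an ICC of 0.05. The ICC matters most: at 0.10, power in all 12 schools is 0.62 for students and 0.74 for teachers. That shows how much rests on the assumption; it does not show that 0.05 is wrong.

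**What to change.** In the Participants section, replace the two minimums with a requirement stated in schools, computed on schools − 2 degrees of freedom at the planned cluster sizes:

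- Students: 12 schools (576 analysed, 720 enrolled).
- Teachers: 11 schools (132 analysed, 165 enrolled at 15 per school).

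Alternatively, hold the 12 schools fixed and give about 414 analysed students and about 112 analysed teachers, with the matching design effects of about 2.68 and 1.42. Use one convention throughout: a design effect for 48 or 12 per school should not be paired with 10 degrees of freedom unless the resulting total is in fact 12 schools.

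In either case, report the power of the full design as 0.84 (students) and 0.86 (teachers) at ICC 0.05, and 0.62 and 0.74 at ICC 0.10.

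The cost is a recalculation and a few sentences. Enrolment, design and targets do not change. The only drawback is that the visible margin looks smaller.
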